#### Secondary outcomes

Secondary outcome measures assessed at 6 and 12 weeks, include:i.7-day point prevalence smoking abstinence, based on: “Have you smoked at least part of a cigarette in the last 7 days?”ii.Point prevalence abstinence from all nicotine (including NRT and ENDs), defined as having not used any products containing nicotine in the previous 7 days at assessment.iii.Continuous abstinence post discharge from all nicotine (including NRT and ENDs).iv.Reported number of cigarettes smoked per day among those who relapse (a relapse is defined as 7 days of continuous smoking for previously daily smokers).v.Cravings, assessed by one item based on Taggar et al. [34]: “Currently, how often do you get strong cravings to smoke tobacco?” with the response options: (1) hourly or more often, (2) several times per day, (3) at least once a day or (4) less than daily.vi.Withdrawal, as assessed by the Minnesota Nicotine Withdrawal Scale [35, 36], an eight-item scale rating withdrawal symptoms on an ordinal scale ranging from 0 (not present) to 4 (severe).vii.Time to relapse, which will be determined for those who do relapse by asking when they first smoked after a quit attempt.viii.Feasibility, which will be assessed by collecting the recruitment rate, consent rate and attrition rate.ix.Acceptability, by asking about the extent of use of the nicotine products provided. This will be determined by a five-point Likert scale administered in the 6- and 12-week surveys. The following question will be asked: “Thinking about your use of and experience with the [product], please indicate your agreement with the following statements: it was effective at reducing my cravings; it was easy to use; it was enjoyable to use.” The response options are: (1) strongly disagree, (2) disagree, (3) undecided, (4) agree or (5) strongly agree. Those in the NRT group will be asked about each type of product individually.x.Number of subsequent quit attempts among those who relapsed.xi.Any adverse events reported during the study.xii.Treatment adherence (use of NRT, ENDs and quitline). Adherence to treatment will be measured by questions about product use in the 6- and 12-week surveys. Participants will be asked if they have used the products and if they are currently using the products. If they are not using the products, then they will be asked why, otherwise they all be asked about the frequency of use and if they use a combination of products.xiii.Process measures. The 6- and 12-week surveys will assess the use of any additional pharmacotherapies, general practice visits and the use of printed and online materials to aid in quitting. Records from the quitline database regarding number, length, content and timing of calls will also be collected. In addition, cost data will be recorded.

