## Abstract

**Background:**

Up to 95% of people entering treatment for use of alcohol or other drugs (AOD) smoke tobacco. Smokers receiving treatment for AOD use are interested in quitting and make quit attempts, but relapse is more common and rapid compared with the general population of smokers. New ways to address smoking in this population are needed. Electronic nicotine devices (ENDs) or electronic cigarettes hold significant potential as both cessation aids and harm reduction support. This study focuses on the potential of ENDs to facilitate smoking cessation and to sustain it in the medium term among people in treatment for AOD use. The aim of this trial is to explore the effectiveness, feasibility and acceptability of ENDs for smoking cessation compared with combination nicotine replacement therapy (NRT) for clients after discharge from a smoke-free AOD residential withdrawal service.

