Following randomisation, the project RA will notify participants of the intervention group they have been assigned to and take them through the contents of the relevant intervention pack. Both groups will receive:Proactive referral to quitline counselling (call-back service), which provides calls at pre-discharge and on days 1, 3, 7, 14 and 28 post-discharge, with an emphasis on relapse prevention. At least one call will be scheduled during their residential withdrawal stay. The total number and timing of calls will be tailored to client need and smoking status (i.e. with more frequent calls around relapse crises and quit attempts). Participants will be sent a text message prior to being called, since AOD clients are unlikely to pick up calls from a private number. Counsellors will be trained on the use of ENDs, will monitor and encourage correct use of NRT and will work with clients to address barriers to their use.A trial business card that contains the study’s toll-free number

The END group will receive:An information pack that includes printed information on the benefits of quitting (including that quitting tobacco may facilitate AOD reduction) and information about nicotine maintenance, the benefits of vaping instead of smoking and the risks of vaping compared to complete abstinence. The lack of data on th health risks of long-term vaping will be highlighted. Instructions on how to use ENDs and safe storage and handling will be included.A 1-week supply of nicotine patches for use while getting used to the END.An END starter kit. The device (Innokin Endura T22 starter kit) and refill liquid (Nicophar) were selected based on quality assurance and compliance with relevant standards.A 4-week supply of liquid nicotine, with further supplies of liquid nicotine mailed to them twice at 4-week intervals.

The NRT group will receive:An information pack like that provided to the END group, but rather than information on ENDs, it will include instructions on how to use NRT correctly and for how long, plus information on potential side effects (and when to notify a health-care provider), safe storage and handling.Provision of 12 weeks of NRT on the same schedule as for ENDs. They will initially receive a 4-week supply of patches plus a nicotine spray and inhaler, which will be followed by refills including patches plus inhaler, gum and lozenges.

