### Outcomes

#### Primary outcome

The primary outcome is the continuous abstinence from smoking (defined using a modified version of the Russell standard [33]), that is, no more than five (tobacco) cigarettes after their discharge from the residential AOD withdrawal service. Sustained abstinence from discharge will be checked at each follow-up time point, i.e. by self-report at weeks 6 and 12. Sustained abstinence will be assessed from the date of the previous interview: “Since [date] did you smoke at all, even part of a cigarette?” and among those who did: “In the past 6 weeks (that is, since [date]), have you smoked a tobacco cigarette, even a puff?” with the response options: (1) no, not a puff, (2) 1–5 cigarettes or (3) more than five cigarettes.

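### The 7-day abstinence item does not say tobacco, so participants who only vape, mainly but not only in the END arm, could be counted as smokers

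*Protocol article*

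**What the plan says.** Under Secondary outcomes, item i of the protocol article defines 7-day point-prevalence smoking abstinence at weeks 6 and 12 from one quoted question: "Have you smoked at least part of a cigarette in the last 7 days". No tobacco qualifier appears, and no follow-up question is shown.

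Two other items name tobacco. The primary outcome uses two steps. A gate question asks "did you smoke at all, even part of a cigarette", also without the word tobacco. Those who answer yes are then asked "have you smoked a tobacco cigarette, even a puff", and the first response option lets them say that they have not had a puff. The cravings item (v) asks "Currently, how often do you get strong cravings to smoke tobacco".

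The Abstract introduces the device as "Electronic nicotine devices (ENDs) or electronic cigarettes", so the two terms are used as equivalents. On the other side, the Procedure section says that the END information pack covers "the benefits of vaping instead of smoking".

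**The concern.** One arm is given a device that is commonly called a cigarette, and the article itself calls it that. A question about having smoked part of a cigarette then leaves an END participant who has stopped tobacco to decide whether vaping counts. If some decide that it does, they are recorded as smokers on item i. The same person could be abstinent on the primary outcome, where the tobacco follow-up can reverse a mistaken yes at the gate.

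Such an error would probably be more frequent in the END arm, because that arm is supplied with the device. It would therefore enter the comparison between arms, beyond adding noise. The Statistical analysis plan section intends relative risks with confidence intervals for all binary variables, and the trial is meant to inform a larger one. With few abstainers per arm, one or two misclassified people would move the estimate.

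**Working it through.** **Plan's own figures.** The article gives no figure for misreading. Its only sample arithmetic, 100 × (1 − 0.40) = 60 at week 12, or 30 per arm, reproduces and is not in question.

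**The items side by side**

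| Item | Names tobacco? | Can a mistaken yes be reversed? |
|---|---|---|
| Primary, gate question | No | Yes, by the next question |
| Primary, follow-up question | Yes | Not applicable |
| 7-day item (i) | No | Not by any step shown |
| Cravings item (v) | Yes | Not applicable |

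**Inputs**
- From the article: 50 per arm; abstinence of 9% to 33% in earlier AOD trials (Background), used only as an illustrative true rate *p*, equal in both arms.
- Assumed, because the article gives neither: *v*, the share of abstainers who vape, and *m*, the probability that an abstinent vaper answers yes.

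**Formula.** Observed abstinence = *p* × (1 − *v* × *m*). With no vaping in the NRT arm, the relative risk is multiplied by 1 − *v* × *m*.

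| *v* (END) | *m* | Multiplier |
|---|---|---|
| 0.5 | 0.05 | 1 − 0.025 = 0.975 |
| 0.7 | 0.10 | 1 − 0.07 = 0.93 |
| 0.7 | 0.30 | 1 − 0.21 = 0.79 |
| any | 0 | 1.00 |

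**In participants.** Expected true abstainers among 50 are 50 × 0.09 = 4.5 to 50 × 0.33 = 16.5. At *v* = 0.7 and *m* = 0.10, the number misclassified is 4.5 × 0.07 = 0.3 to 16.5 × 0.07 = 1.2. At *m* = 0.30 it is 4.5 × 0.21 = 0.9 to 16.5 × 0.21 = 3.5.

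**If NRT participants vape too.** With *v* = 0.8 in END, *v* = 0.2 in NRT and *m* = 0.20, the multiplier is (1 − 0.16) / (1 − 0.04) = 0.84 / 0.96 = 0.875. With no NRT vaping it is 0.84. The effect is smaller and in the same direction.

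**Opposite error.** False claims of abstinence by END smokers alone would cancel the misreading if their rate were *p* × *v* × *m* / (1 − *p*). At *v* = 0.8 and *m* = 0.20:
- *p* = 9%: 0.0144 / 0.91 = 1.6%
- *p* = 33%: 0.0528 / 0.67 = 7.9%

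**The case against.** A reader might infer that only END participants can be misclassified and that the outcome is therefore biased against ENDs. The document does not support either step. The Exclusion criteria bar nicotine END use only in the month before entry, and no rule against vaping by NRT participants during follow-up is stated. Any vaper could misread the item. The trial is also open-label with unverified self-report, so false claims of abstinence may differ by arm as well. As the last calculation shows, a modest rate of these would cancel a 20% misreading rate. The net direction is undetermined.

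The contrast with the primary outcome is also less clean than it may look, because its gate question omits tobacco too. What protects the primary outcome is the second step.

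Several features lower the risk of misreading. The outcome is labelled as smoking abstinence and the verb is to smoke. The device is a refillable kit, and the research assistant takes each participant through a pack that contrasts vaping with smoking. The phrase that equates ENDs with electronic cigarettes stands in the Abstract and addresses readers of the article. Item i is described as based on the quoted question, so a preamble or definition in the full questionnaire cannot be ruled out.

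These points stand, and they limit the size and certainty of the problem. They do not remove the gap. The article prints the question as the basis of the outcome, and its section on electronic nicotine devices itself likens the inhaled and exhaled vapour to smoke. The possibility of an opposing error is no reason to keep one that can be removed by rewording.

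**Conclusion.** The point holds in a limited form. Item i lacks the tobacco qualifier used elsewhere in the same survey and has no corrective step. Participants who only vape, expected mainly but not only in the END arm, could therefore be counted as smokers. Taken alone, this would lower the END arm's 7-day abstinence.

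The size cannot be derived from the document. The multipliers of about 0.98 to 0.79 rest on assumed vaping shares of 50% to 70%, misreading rates of 5% to 30% and no vaping in the NRT arm. If nobody misreads the item, there is no bias. A claim that the outcome is in fact biased against ENDs would go further than the document allows.

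This is a minor point about one secondary outcome in an exploratory pilot. The primary outcome is largely protected by its tobacco follow-up question.

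**What to change.** **Wording.** In item i, and for consistency in the primary gate question, ask about a tobacco cigarette, not counting e-cigarettes or vaping. If the full questionnaire already carries such a definition, stating it in the article is enough.

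**Surveys already completed.** Apply one consistency rule, blinded to arm. Code as 7-day abstinent anyone who answers yes to item i but, in the same survey, either
- answers no at the primary gate question, or
- answers yes at the gate and then reports not a puff at the tobacco follow-up.

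Both branches are needed, because those who answer no at the gate never see the tobacco question. Both primary questions run up to the interview and so cover the last 7 days. Leave anyone who reports 1–5 or more than five cigarettes as answered: those cigarettes may or may not fall within the last 7 days, and the rule cannot tell.

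**Reporting.** The rule moves people only toward abstinence, so give the number recoded in each arm and the 7-day result with and without recoding.

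**Cost.** One wording change, one data-cleaning rule and one extra result. Recruitment began in August 2017, so item wording may be mixed within a small sample; a version flag in the data set handles this.

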A recent Cochrane review found that ENDs are effective, but not necessarily more effective than other forms of NRT [27]. The authors concluded that this was due to a lack of evidence and recommended more studies be conducted. Trials with smokers in the general population have demonstrated the safety and efficacy of ENDs compared to other forms of NRT. In New Zealand, one study found that verified abstinence rates at 6 months were 7.3% for early-generation low-nicotine-delivery ENDs, 5.8% for NRT patches and 4.1% for placebo ENDs [28]. Cigarette consumption was reduced by at least half in 57% of the participants allocated to nicotine ENDs vs 41% in the patches group and 45% in the placebo group. Median time to relapse was twice that in participants allocated to nicotine ENDs than patches or the placebo. No significant differences in adverse events were observed. A secondary analysis of participants with mental illness found no differences between END and NRT for rates of relapse, but the e-cigarette group had higher levels of smoking reduction, treatment adherence and acceptability [29]. Further, a longitudinal study in the USA found that at the 2-year follow-up, long-term ENDs users had a higher cessation rate (42.4%) than short-term users (14.2%) or non-users (15.6%). Also, for those participants reporting quit attempts, significantly more reported using ENDs as a cessation aid (24.8%) than reported using an FDA-approved NRT (17.8%) [30]. A similar study with people on methadone maintenance therapy found no difference in the effectiveness of e-cigarettes and NRT [29]. Another in people living with mental illness found self-reported combustible tobacco use and breath CO significantly declined among those using an e-cigarette [30]. However, most studies so far have been with small participant numbers or have focused on short-term timeframes. More evidence gathered from well-controlled studies with larger sample sizes to inform policy and practice regarding END use is needed, particularly of the likelihood that alternative forms of nicotine will be taken up as cessation aids or harm reduction tools, and with populations with high smoking prevalence and low quit rates.

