#### Statistical analysis plan

Data will be collected on recruitment and retention rates, which will aid the design of future larger trials. Primary cessation outcome analyses will be carried out on an intention-to-treat basis. We will use chi-squared tests to compute relative risks, 95% confidence intervals and two-sided *p* values for all binary variables, followed by adjusted multiple logistic regression analyses. Continuous outcomes (with 95% confidence intervals) will be analysed using generalised linear mixed methods regression for the main aims, with adjustments for covariates where necessary.

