The current study is not powered to detect small differences in cessation; however, it will provide valuable information on the feasibility, acceptability and potential effectiveness of ENDs as a smoking cessation and harm reduction aid with AOD populations, and inform the design of a larger, powered study. It will also provide safety and adverse events data. The project also lacks a no-intervention placebo, control group. However, the combination NRT group represents current best practice and this study was designed to test the feasibility of ENDs in this population compared with current best practice and to inform future larger-scale studies. Another limitation is that the study utilises self-reported cessation rather than any biomarker confirmation. Biochemical verification is recommended for studies using the Russell standard as an outcome measure [51]; however, experts have agreed that biochemical validation methods need not always be used to validate self-report smoking cessation measures [52]. While it is possible to include biochemical verification in a trial such as this, the limited funding available made it difficult to do so. Following consultation between all study investigators, it was decided that given the aims of the pilot trial were to test the acceptability and feasibility of ENDs, and the study is not powered to determine the effectiveness of smoking cessation (which would be the primary reason for biochemical verification), that the additional cost and resources (in staff time) required to complete the biochemical verification were not warranted. Note that the study authors have submitted a funding application for an adequately powered effectiveness randomised controlled trial, which will assess biochemically verified smoking cessation as the primary aim.

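### Cigarettes per day is defined only among people who relapse, so an arm comparison of it is not randomised and leaves out smoking avoided through abstinence

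*Protocol article*

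**What the plan says.** Under Secondary outcomes, item iv of the Protocol article is "Reported number of cigarettes smoked per day among those who relapse", where "a relapse is defined as 7 days of continuous smoking for previously daily smokers". Item x has the same restriction: "Number of subsequent quit attempts among those who relapsed". No other listed outcome measures the amount smoked. Items i to iii are abstinence outcomes and item vii is time to relapse among those who relapse.

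The primary outcome allows "no more than five (tobacco) cigarettes after their discharge from the residential AOD withdrawal service". The Statistical analysis plan section states that "Primary cessation outcome analyses will be carried out on an intention-to-treat basis", and that "Continuous outcomes (with 95% confidence intervals) will be analysed using generalised linear mixed methods regression for the main aims", with covariate adjustment if needed. It does not say how an outcome that exists only for a subset formed after randomisation is to be handled.

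The Discussion says the study will inform on the "potential effectiveness of ENDs as a smoking cessation and harm reduction aid with AOD populations". The Background reports the reduction result of an earlier trial over everyone allocated: "Cigarette consumption was reduced by at least half in 57% of the participants allocated to nicotine ENDs".

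**The concern.** Randomisation makes the two arms comparable, but not the relapsers in one arm with the relapsers in the other. If ENDs prevent more relapse than NRT, the two subsets differ in who is left, and the treatment itself has made them differ. The protocol's Background names heavy nicotine dependence as a contributor to relapse, so a link between consumption and relapse is plausible. If lighter smokers are the ones kept from relapse, END relapsers will be heavier smokers on average. If ENDs mainly help heavier smokers, the bias runs the other way.

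The definition also leaves people out. Someone who smokes more than five cigarettes, but never seven days running, fails the primary outcome and is still not a relapser. Inclusion asks only for a tobacco smoker on entry, and the relapse definition covers only previously daily smokers. These participants have no value under iv, yet partial reduction among them is part of what a harm reduction question asks about.

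At stake is whether the pilot can say anything, on a randomised basis, about how much each arm smokes.

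**Working it through.** **The plan's own figure.** 100 recruited with 40% attrition gives 100 × (1 − 0.40) = 60, or 30 per arm, as the Sample size estimation section states. The protocol gives no effect size or standard deviation for cigarettes per day, so there is nothing further to reproduce.

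**How many would enter the comparison.** The Background cites abstinence of 9% to 33% in earlier AOD trials. Of 30 completers per arm, 30 × 0.91 ≈ 27 down to 30 × 0.67 ≈ 20 would not be abstinent. Relapsers by the seven-day definition would be fewer still.

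**Hand check in two strata (all inputs assumed).** Half the participants smoke 10 a day if relapsed and half smoke 25. Relapse in light/heavy smokers is 80%/95% on NRT and 55%/90% on END. ENDs change no relapser's consumption.

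- NRT: total per person randomised = 0.5×0.80×10 + 0.5×0.95×25 = 15.9. Relapse rate = 0.875. Relapser mean = 15.875/0.875 = 18.1.
- END: total = 0.5×0.55×10 + 0.5×0.90×25 = 14.0. Relapse rate = 0.725. Relapser mean = 14.0/0.725 = 19.3.
- Relapsers only: END is 1.2 worse. All randomised, non-relapsers at 0: END is 1.9 better.

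**Simulation (all inputs assumed).** Baseline is log-normal with median 18 a day and log SD 0.5. The log-odds of abstinence fall by 1 per SD of log consumption. Everyone still smoking cuts down by 30% in both arms, and every non-abstainer is treated as a relapser.

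| Abstinence NRT vs END | Relapsers only, NRT vs END | END − NRT | All randomised, NRT vs END | END − NRT |
|---|---|---|---|---|
| 10% vs 30% | 14.8 vs 15.9 | +1.1 | 13.3 vs 11.1 | −2.2 |
| 10% vs 20% | 14.8 vs 15.4 | +0.5 | 13.3 vs 12.3 | about −1.0 |

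**Sensitivity at 10% vs 30%.**

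- Slope 0 (consumption unrelated to quitting): relapsers 0.0, all randomised −2.9.
- Slope 0.5: relapsers +0.6, all randomised −2.5.
- Slope 1.5: relapsers +1.4, all randomised −2.0.
- Slope 1, adjusting for the four cigarettes-per-day bands of the Heaviness of Smoking Index: +1.1 falls to about +0.1. With a continuous baseline it is 0, because selection here acts only through baseline consumption.

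**If ENDs also reduce relapsers' smoking.** A second simulation assumed baseline mean 20 and SD 8, NRT abstinence 9% or 33%, END abstinence 1.5 or 2 times that, and a correlation of 0, 0.3 or 0.5 between consumption and failing to abstain. With a 5% cut in END relapsers, the sign reverses only at 33% vs 66% abstinence (+0.2 at correlation 0.3, +0.9 at 0.5). With a 10% cut it never reverses. The all-randomised contrast favours ENDs in every scenario.

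**Precision.** At 10% vs 30%, 30 completers per arm leave 27 and 21 relapsers. The simulated SDs are about 7.7 and 7.9, so SE = √(7.7²/27 + 7.9²/21) ≈ 2.3 cigarettes/day.

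**The case against.** The protocol lists iv as an outcome but states no between-arm test of it. Intention-to-treat is attached to the primary cessation analyses, the mixed regression is tied to the main aims, and a fuller analysis plan may exist. Descriptive reporting of iv would be compatible with the text. That stands, and it limits the point to what any arm comparison of iv could mean. The restriction itself is part of the stated outcome definition, so it is not a detail left to another document.

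The plan allows covariate adjustment and lists smoking history and the Heaviness of Smoking Index as covariates. Under the illustration's own assumptions, adjustment removes nearly all of the apparent harm. That also stands. It would not remove selection on unmeasured factors, and an adjusted contrast near 0 still says nothing about cigarettes avoided by people who abstain.

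Abstinence is already captured by the primary outcome, so iv might be seen as a supplement to it. That is fair for full abstainers. It does not help those who smoke intermittently, who count as failures on the primary outcome and are absent from iv.

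This is one of 13 secondary items in a pilot that says it is not powered for cessation effectiveness. The primary result is untouched.

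**Conclusion.** The point holds as a flaw in the definition of a secondary outcome. Item iv, the only listed measure of amount smoked, does not compare the randomised groups, omits reduction through abstinence, and leaves some smokers without a value. The robust part is that the relapser contrast misses the benefit: at 10% vs 30% abstinence it lies between 0 and about +1.4 across the slopes tried, against −2.0 to −2.9 over all randomised. These sizes rest on assumed consumption, abstinence and selection, and on treating every non-abstainer as a relapser.

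Three stronger readings are not supported.

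- A reader might infer that iv will point the wrong way. Reversal needs an END effect on relapse, lighter smokers being the ones who avoid it, no baseline adjustment, and little or no END effect on relapsers' own smoking. Even then a shift of 1.1 is about half a standard error.
- A reader might infer that iv is the protocol's harm reduction outcome. No section gives it that label, and the Aim does not name harm reduction. The Discussion says only that the study will inform on it, and leaves the powered assessment to a larger trial.
- A reader might infer that item x should be redefined in the same way. Quit attempts after relapse have no meaning for people who never relapsed. The caution for x is only against testing it between arms.

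**What to change.** - Define iv as current cigarettes per day at 6 and 12 weeks in all randomised participants, with 0 for those who report not smoking. People lost to follow-up are missing, not 0.
- Adjust for baseline consumption, using the Heaviness of Smoking Index bands, or a count if one is recorded.
- Report relapser-only cigarettes per day and quit attempts (x) descriptively, without a between-arm test.
- Add an outcome of at least 50% reduction only if a numeric baseline count is recorded. The Covariate measures section shows the item in four bands (1–10, 11–20, 21–30, 31+), from which a halving cannot be computed.

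Cost: new outcome wording, analysis code, and asking the cigarettes-per-day item of everyone who reports any smoking. Recruitment began on 1 August 2017, so this is a small change to a survey already in use. If the item was asked only of relapsers, participants already followed up will lack it and the report should say so.
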